# Total neoadjuvant therapy followed by a watch-and-wait strategy for patients with rectal cancer (TOWARd): protocol for single-arm phase II/III confirmatory trial (JCOG2010)

**DOI:** 10.1093/bjsopen/zrad110

**Published:** 2023-11-01

## Abstract

**Background:**

Radical surgery is the standard treatment for rectal cancer, but can impact quality of life. Recently, the concept of total neoadjuvant therapy with a watch-and-wait strategy has been proposed in which patients with a cCR after total neoadjuvant therapy do not proceed to surgery. However, most investigations of a watch-and-wait strategy have reported cases where cCR was achieved coincidentally via total neoadjuvant therapy. The aim is to assess whether total neoadjuvant therapy is effective in early-stage rectal cancer in patients that achieve cCR and are offered a watch-and-wait strategy.

**Methods:**

JCOG2010 (TOWARd) is a multi-institutional, single-arm phase II/III confirmatory investigation of the safety and efficacy of total neoadjuvant therapy followed by a watch-and-wait strategy for rectal cancer. Key eligibility criteria include cT2–3 N0 M0 rectal adenocarcinoma, tumour diameter less than or equal to 5 cm, age 18–75 years, performance status 0–1, and no history of pelvic irradiation or rectal surgery. Total neoadjuvant therapy involves neoadjuvant chemoradiotherapy (capecitabine and radiotherapy: 45 Gy/25 fractions to the whole pelvis plus boost of 5.4 Gy/3 fractions to the primary tumour) followed by consolidation chemotherapy (four cycles of capecitabine/oxaliplatin). Patients will be re-staged every 8 weeks after total neoadjuvant therapy, and those who achieve cCR will undergo a watch-and-wait strategy, those with near complete response will undergo a watch-and-wait strategy or local resection, and those with an incomplete response will undergo radical surgery. The primary endpoint is the cCR rate in phase II and 5-year overall survival in phase III. Secondary endpoints include postoperative anal, urinary, and sexual function. A total of 105 patients (phase II, 40 patients; phase III, 65 patients) will be enrolled over 3.5 years.

**Conclusion:**

This trial will determine whether total neoadjuvant therapy and a watch-and-wait strategy is an effective alternative to radical surgery for early-stage rectal cancer in patients with cT2–3 N0 M0 and tumour size less than or equal to 5 cm.

**Registration number:**

jRCTs031220288 (https://jrct.niph.go.jp/en-latest-detail/jRCTs031220288).

## Introduction

Rectal cancer (RC) is the eighth leading cause of cancer-related mortality worldwide^1^. The standard treatment for cT2–3 N0 M0 RC in Japan is surgical resection followed by postoperative chemotherapy. However, some patients with RC who undergo surgery experience a considerable decline in postoperative quality of life (QoL), including frequent defaecation, need for a temporary/permanent colostomy as a result of rectal resection, and urinary or sexual dysfunction as a consequence of autonomic nerve damage during the procedure^2,3^. The perioperative treatment strategy for stage II/III RC varies among different guidelines. The European Society for Medical Oncology (ESMO) guidelines recommend upfront total mesorecta excision for T3a/b Nany^4^, whereas the American Society of Clinical Oncology (ASCO) guidelines recommend preoperative chemotherapy with radiation for patients with elevated risk profiles of local regional recurrence in the pelvis^5^. Furthermore, the concept of total neoadjuvant therapy (TNT) followed by a watch-and-wait strategy (W&W) has been put forward in recent years, in which surgery is not required in patients who have a cCR after TNT^6–9^. However, the cCR rate has varied considerably in different trials due to variability in the target population and in the response evaluation criteria used. Therefore, patients who are suitable for W&W and the cCR rate achieved by TNT remain to be determined.

TNT, which includes neoadjuvant chemoradiation and preoperative chemotherapy, is presently being advanced in the USA and Europe with the objective of improving the local anti-tumour effect by integrating neoadjuvant chemoradiotherapy (nCRT) and the distant anti-tumour effect by systemic chemotherapy. A previous investigation assessed multiple courses of a modified FOLFOX (fluorouracil/leucovorin plus oxaliplatin) regimen for consolidation chemotherapy and found that the pCR rate in resected specimens increased with the duration of treatment^10^. Therefore, in the upcoming JCOG2010 study, TNT rather than nCRT alone will be used to increase the pCR rate. In the CAO/ARO/AIO-12 trial, which compared the efficacy of induction *versus* consolidation chemotherapy in patients with locally advanced RC, the pCR rate was higher in the consolidation chemotherapy group than in the induction chemotherapy group (27 *versus* 19 per cent respectively) and the incidence of grade 3–4 adverse events was higher in the induction chemotherapy group than in the consolidation chemotherapy group (37 *versus* 27 per cent respectively)^11,12^. Therefore, the JCOG2010 study will investigate TNT with nCRT followed by consolidation chemotherapy.

A phase III trial conducted in Germany demonstrated that oral capecitabine was non-inferior to 5-fluorouracil/leucovorin for locally advanced RC^13^. Capecitabine is the chemotherapy most used in combination with radiotherapy worldwide, including in Japan^14^. Therefore, JCOG2010 will use oral capecitabine alone as the chemotherapy regimen in combination with radiotherapy. In terms of radiotherapy, the National Comprehensive Cancer Network guidelines suggest that the pelvic cavity should be irradiated at a dose of 45 Gy/25 fractions with primary tumour boost irradiation at 5.4 Gy/3 fractions as the treatment approach in nCRT^15^, which will be used in this study. With regard to the consolidation chemotherapy regimen, the CAO/ARO/AIO-12 trial, which administered six cycles of FOLFOX after nCRT, reported that 22 per cent of patients experienced grade 3 or higher adverse events during consolidation chemotherapy. Although there are no reports comparing FOLFOX with CAPOX (capecitabine/oxaliplatin) as a preoperative treatment, both are commonly used in clinical practice and are effective as adjuvant chemotherapy for colon cancer^16^. In view of its convenience, CAPOX has been chosen as the protocol treatment in this trial. FOLFOX is administered as six cycles at 2-week intervals over 12 weeks and CAPOX as four cycles at 3-week intervals over 12 weeks. Given the comparable efficacy of these regimens as adjuvant chemotherapy, four cycles of CAPOX will be used as consolidation chemotherapy in the JCOG2010 study.

The aim of this multi-institutional, single-arm phase II/III trial is to examine the safety and efficacy of TNT followed by W&W in patients with early-stage RC and high potential for non-operative management.

## Methods

### Overall study design

JCOG2010 is a multi-institutional, single-arm phase II/III trial that is designed to confirm that TNT followed by W&W is non-inferior to the standard therapy of surgical resection with lymph node dissection for cT2–3 N0 M0 RC. The primary objective of the phase III component is to confirm that TNT followed by W&W, which is less invasive and may avoid the need for colostomy, is non-inferior to the standard treatment of surgical resection for RC by comparing the 5-year overall survival (OS) rate in the TNT and W&W group with that in a historical control group.

A randomized phase III trial comparing the efficacy of TNT and W&W with that of surgical resection with lymph node dissection was not opted for, in view of the findings of JCOG0212, which reported a 5-year OS rate of 95.3 per cent for patients with cT3 N0 M0 disease and a tumour diameter of less than or equal to 5 cm^3,17,18^. It is unlikely that the 5-year OS rate would be less than 95 per cent in the standard treatment group, given that cT2 N0 M0 is associated with a better prognosis than cT3 N0 M0. Even without randomized controls, the efficacy of the study treatment could be established if the 5-year OS rate in the TNT and W&W group is non-inferior to 95 per cent. Therefore, a randomized trial would be of limited value, and a single-arm study design has been selected. The study schema is shown in *Fig. 1*.

**Fig. 1 zrad110-F1:**
[figure not shown]
Schema for the JCOG2010 study Patients initially undergo neoadjuvant chemoradiotherapy (using capecitabine and a total irradiation of 50.4 Gy/28 fractions), and thereafter the first response evaluation is performed. If there is no apparent progressive disease or new tumour lesion, consolidation chemotherapy (four cycles of CAPOX (capecitabine/oxaliplatin)) will be implemented. After consolidation chemotherapy, three treatment strategies, including W&W, local resection, or radical surgery, will be considered according to the results of the response evaluation (that is cCR, near complete response, or incomplete response). W&W must be carried out until disease progression or relapse is detected. PS, performance status; RT, radiotherapy; PD, progressive disease; CR, complete response; W&W, watch-and-wait strategy.

In this study, the response will be evaluated according to the Memorial Sloan Kettering Cancer Center (MSKCC) criteria, which were initially proposed by the MSKCC and used in OPRA, a phase II trial that assessed the usefulness of W&W^19^. These criteria pertain only to primary tumours in the rectum and regional lymph nodes, so cannot be used to assess other lesions. Patients are classified into three response categories: cCR, near complete response (near CR), or incomplete response.

### Participants

#### Eligibility criteria

Patients must meet all of the following criteria: endoscopic biopsy from a primary rectal lesion histologically diagnosed as tubular adenocarcinoma (well or moderately differentiated) or endoscopic biopsy from a primary lesion in the anal canal histologically diagnosed as adenocarcinoma (rectal type) and further diagnosed as well or moderately differentiated; the tumour is located predominantly in the upper rectum, lower rectum, or anal canal; the lower margin of the tumour is located between the peritoneal reflection and the anal verge (lower rectum–anal canal); comprehensive diagnosis of cT2–cT3 by abdominal and pelvic contrast CT and pelvic contrast MRI with a slice thickness of less than or equal to 5 mm (Japanese Society for Cancer of the Colon and Rectum guidelines, ninth edition)—if contrast-enhanced CT or contrast-enhanced MRI is not possible because of allergy, renal dysfunction, or bronchial asthma, plain CT or plain MRI is acceptable; no lymph node satisfying either a or b below is present on comprehensive diagnosis by contrast-enhanced CT of the chest, abdomen, and pelvic region with a slice thickness of less than or equal to 5 mm and contrast-enhanced MRI of the pelvic region (a, 10 mm or more in short diameter; b, 7 mm or more in short diameter and one or more of the following: irregular margins, internal inhomogeneous low-signal areas shown on MRI, and circular (long to short diameter ratio less than 1.5)); no distant metastasis; maximum tumour diameter less than 5 cm on comprehensive diagnosis by contrast-enhanced CT of the abdomen and pelvis with a slice thickness of less than or equal to 5 mm, contrast-enhanced MRI of the pelvis, and endoscopy of the lower gastrointestinal tract; comprehensive diagnosis using colonoscopy and imaging studies (barium enema or abdominal/pelvic contrast CT or CT colonography) does not reveal multiple carcinomas (however, cTis and cT1a (cancer expected to remain in the submucosal layer and invade by less than 1000 µm) lesions that are expected to be curatively treated by endoscopic resection are not considered multiple carcinomas); aged between 18 and 75 years on the date of enrolment; Eastern Cooperative Oncology Group performance status 0 or 1; the patient does not wish to undergo surgical resection (that is the standard of care) as initial treatment, but wishes to undergo salvage treatment, including surgical resection, in the event of residual or recurrent disease; oral intake possible; no history of rectal resection (except for endoscopic resection), radiation therapy to the pelvic region, or any previous treatment, including for other types of cancer; the most recent laboratory test values within 14 days before registration include neutrophil count greater than or equal to 1500/mm^3^, haemoglobin greater than or equal to 9.0 g/dL, platelet count greater than or equal to 100 000/mm^3^, total bilirubin less than or equal to 2.0 mg/dL, aspartate transaminase less than or equal to 100 U/L, alanine transaminase less than or equal to 100 U/L, and serum creatinine less than or equal to 1.5 mg/dL; and able to provide written informed consent.

#### Exclusion criteria

Patients with any of the following are excluded: synchronous or metachronous (within 5 years) malignancy except for cancer with a 5-year relative survival rate of greater than or equal to 95 per cent, such as carcinoma *in situ*, intramucosal tumour, or early-stage cancer; infectious disease requiring systemic treatment; body temperature greater than or equal to 38.0°C at the time of registration; women who are pregnant, within 28 days postpartum, or lactating, and men whose partners wish to become pregnant; severe psychiatric disease affecting everyday life; receiving continuous systemic corticosteroids or immunosuppressive agents; poorly controlled diabetes mellitus; uncontrolled hypertension; history of unstable angina pectoris within 3 weeks or myocardial infarction within 6 months before registration; poorly controlled valvular heart disease, dilated cardiomyopathy, or hypertrophic cardiomyopathy; hepatitis B surface antigen positive; human immunodeficiency virus antibody positive; and having one or more of interstitial pneumonia, pulmonary fibrosis, or severe emphysema diagnosed by chest CT.

### Interventions

#### Neoadjuvant chemoradiotherapy

In this study, nCRT consists of oral capecitabine at a dose of 1650 mg/m^2^/day for 28 days and irradiation of the pelvic cavity at a dose of 45 Gy/25 fractions with boost irradiation of the primary tumour at 5.4 Gy/3 fractions. Intensity-modulated radiation therapy (IMRT) and three-dimensional conformal radiation therapy (3D-CRT) can be used in medical facilities that comply with the requirements for use of these modalities. It is permissible to apply IMRT at a dose of 45 Gy/25 fractions to the pelvic region followed by a switch to 3D-CRT at a dose of 5.4 Gy/3 fractions to intensify treatment of the primary tumour. It is not deemed acceptable to change the method of irradiation while irradiating the pelvic region.

#### Consolidation chemotherapy

After completion of nCRT, the first response evaluation is performed on days 8–21, with the final day of irradiation being day 0. If there is no apparent progressive disease or new tumour lesion, consolidation chemotherapy will be implemented. Conversely, if tumour progression is detected, radical surgery will be undertaken.

Consolidation chemotherapy involves administration of four cycles of CAPOX, which comprises capecitabine at a dose of 2000 mg/m^2^/day for 14 days in combination with oxaliplatin at a dose of 130 mg/m^2^ on day 1, starting on day 21 after the last irradiation. Even if consolidation chemotherapy is not possible because of nCRT-related adverse events, it may be initiated as a protocol therapy until day 35.

#### Evaluation of response after consolidation chemotherapy to determine whether the subsequent treatment strategy should be a watch-and-wait strategy, radical surgery, or local resection

After consolidation chemotherapy, the second response evaluation is performed on days 28–43, with day 0 being the last day of the fourth course of CAPOX. For patients who have not completed consolidation chemotherapy, the second response evaluation is performed on days 28–43, with the final day of consolidation chemotherapy being day 0.

If the second response evaluation indicates cCR, W&W is chosen. However, if the response is deemed to be incomplete, radical surgery is performed. Subsequent response evaluations are scheduled to be conducted no more than twice every 8 weeks for patients achieving near CR. According to the results of the response evaluation, one of the three types of treatment, namely W&W, local resection, or radical surgery, is selected. If distant metastasis occurs, the protocol treatment is terminated, and post-study treatment is not regulated.

#### Watch-and-wait strategy: non-operative follow-up

W&W is initiated for patients who achieve cCR at any of the second to fourth response evaluations or near CR at the fourth response evaluation (regarded as the final response evaluation) and express willingness to undergo W&W after consulting with a primary physician. W&W should be carried out until disease progression or relapse is detected. After the final response evaluation, follow-up should be conducted at 12-week intervals for 2 years and at 24-week intervals for 3 years thereafter. In the event of recurrence or progression of the primary tumour or involvement of regional lymph nodes, radical surgery is recommended as off-protocol treatment.

#### Radical surgery

For patients who are judged to have an incomplete response at any response evaluation or near CR at the final evaluation, but express willingness to undergo radical surgery after consulting with a primary physician, the procedure will be carried out within 2–14 weeks from the final evaluation provided that both of the following criteria are met: the patient should be suitable for R0 resection, as determined by preoperative imaging tests; and the following laboratory criteria are met within the 14 days preceding radical surgery—white blood cell count greater than or equal to 3000/mm^3^ and platelet count greater than or equal to 100 000/mm^3^.

If the first response evaluation reveals tumour progression or distant metastasis that is considered amenable to R0 curative surgery, radical surgery is recommended as off-protocol treatment. Off-protocol radical surgery is also recommended for patients in whom nCRT is discontinued for whatever reason, but curative R0 resection is still considered feasible.

#### Procedures

Radical surgery may consist of total mesorectal excision or tumour-specific mesorectal excision, both of which are considered standard procedures. Addition of lateral lymph node dissection is not specified. Open, laparoscopic, or robotic-assisted procedures are all acceptable.

#### Local resection

For patients who are judged to have near CR at the final response evaluation and are willing to undergo local resection after consulting with a primary physician, the procedure will be performed within 2–14 weeks from the date of the final response evaluation, provided that the following preoperative laboratory criteria are met: white blood cell count greater than or equal to 3000/mm^3^; and platelet count greater than or equal to 100 000/mm^3^.

#### Procedures

Local resection will be performed as transanal surgical resection using an appropriate technique (for example transanal endoscopic microsurgery or transanal minimally invasive surgery) or as transanal endoscopic resection (for example endoscopic mucosal resection or endoscopic submucosal dissection).

### Outcomes

#### Phase II component

The primary endpoint of the phase II component is the proportion of patients with cCR at the final response evaluation (as assessed by central review to enhance the robustness of the final assessment).

The secondary endpoints in phase II are the proportion of patients with a clinical/near CR at the final response evaluation (by central review), the proportion of patients who do not undergo resection of the rectum, adverse events, the incidence of surgical morbidities, and the concordance of response evaluation between the central review and the institutional in-house review.

The final response evaluation is the point when a patient achieves cCR or the fourth response evaluation, whichever is earliest. The proportions of patients with cCR or cCR/near CR are defined according to the MSKCC criteria and include all eligible patients. The proportion of patients who do not undergo rectal resection is defined as the proportion treated with W&W or local resection and includes all eligible patients. Adverse events associated with preoperative CRT and consolidation chemotherapy are assessed in accordance with the Common Terminology Criteria for Adverse Events (CTCAE) version 5.0. Surgical morbidities are evaluated according to CTCAE version 5.0 and the Clavien–Dindo classification^20^. Concordance of response evaluation between the central review and the institutional in-house review is calculated.

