#### Phase III component

The primary endpoint of the phase III component is OS in all enrolled patients. OS is defined as the time interval between registration and death from any cause, and data are censored on the last day the patient is alive. The secondary endpoints include progression-free survival, local progression-free survival, rectal resection-free survival, colostomy-free survival, the proportion of patients with cCR at the final response evaluation (by central review), the proportion of patients with cCR/near CR at the final response evaluation (by central review), the proportion of patients who do not undergo rectal resection, adverse events, incidence of surgical morbidities, concordance of response evaluation between the central review and the institutional in-house review, the proportion of patients with R0 resection among those who undergo radical surgery, the proportion of patients with tumour progression among those who undergo W&W, defecation and anal function (Wexner and Low Anterior Resection Syndrome scores^21,22^), urinary outcomes (International Prostate Symptom score^23^), and sexual function in male patients (score on the five-item version of the International Index of Erectile Function^24^). Progression-free survival is defined as the time interval between registration and disease progression (including events after cCR/near CR or radical surgery) or death from any cause. The data are censored on the last day the patient is alive without any evidence of disease progression. Wexner and International Prostate Symptom scores and the score on the five-item version of the International Index of Erectile Function^24^ are evaluated before treatment and at 1 year and 5 years after registration.

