The cCR rate achieved by nCRT for cT3N0 rectal carcinoma, which is associated with feasibility of preserving the rectum, was noted to be 54.2 per cent when the two-classification system (cCR or incomplete response) was used^29^. Despite focusing on patients with cT2 N0 M0 disease, the present study considers addition of consolidation chemotherapy as TNT, which could potentially augment the cCR rate. However, the assessment criteria for treatment response entail a three-classification system (cCR, near CR, or incomplete response). It is plausible that some patients in this study who would be previously identified as having cCR could be classified as having near CR. The expected cCR and near CR rates in this study have therefore been set at 40 and 20 per cent respectively. In view of the lower probability that patients categorized as having near CR would opt for radical surgery and data from a previous report^30^, around 60 per cent of patients classified as having near CR would be expected to select W&W and 40 per cent would opt for local resection. In summary, W&W would be performed for 52 per cent of patients and local resection for 8 per cent of patients in the JCOG2010 study. Assuming that approximately 40 per cent of local resection cases and 20 per cent of W&W cases will undergo radical surgery for residual tumour or local progression, rectal preservation would ultimately be expected in 45.4 per cent of patients in the present study.

This study will include a longitudinal evaluation of anal and defecation function, urinary function, and sexual function in men. If rectal preservation by TNT and W&W is practicable, these functions may be expected to be preserved. However, there is currently no information on the degree to which TNT affects these functions, and the longitudinal analysis may provide fundamental data for clinical research and enable informed decision-making when TNT is implemented in clinical practice. An ancillary study is also planned to assess the potential value of circulating tumour DNA as a marker for therapeutic and prognostic purposes in patients with RC who are treated with TNT followed by W&W. Correlating the findings of the ancillary study with those of the present study could significantly influence clinical practice and advance the field of personalized and precision medicine.

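### The secondary endpoint named for patients without rectal resection is defined by treatment received, so, read literally, it keeps patients resected later in its numerator

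*Protocol article*

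**What the plan says.** Under Outcomes, Phase II component, the protocol article lists the proportion of patients without resection of the rectum as a secondary endpoint and defines it: "The proportion of patients who do not undergo rectal resection is defined as the proportion treated with W&W or local resection". The population is fixed in the same sentence: "treated with W&W or local resection and includes all eligible patients". No time point is attached, and the sentence does not say what happens to a patient whose rectum is removed afterwards.

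The Phase III component section lists "the proportion of patients who do not undergo rectal resection" again among its secondary endpoints and does not redefine it. The same list contains rectal resection-free survival and colostomy-free survival. The phase II list contains neither.

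The section on non-operative follow-up states that, on regrowth or nodal involvement during W&W, "radical surgery is recommended as off-protocol treatment". The Discussion expects such surgery to be common: it assumes that about "40 per cent of local resection cases and 20 per cent of W&W cases will undergo radical surgery" for residual tumour or local progression.

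**The concern.** The name of the endpoint describes an outcome: the rectum was not resected. The definition describes a treatment category: the patient was treated with W&W or local resection. The two agree only while nobody in that category is resected later. A patient who has off-protocol surgery for regrowth was nonetheless treated with W&W, and nothing in the definition reclassifies that patient.

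Avoiding rectal resection is the benefit the trial offers. The sample size section sets the 5-year OS threshold at 87% against an expected 95%, on the ground that roughly half of the patients would be spared radical surgery. A proportion that does not fall when patients are resected would make that benefit look larger than it is. In phase III, with at least 5 years of follow-up, it would stand beside a time-to-event endpoint of nearly the same name that does register those resections.

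**Working it through.** All inputs come from the Discussion of the protocol article.

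- Response rates: "The expected cCR and near CR rates in this study have therefore been set at 40 and 20 per cent respectively".
- Choice after near CR: "around 60 per cent of patients classified as having near CR would be expected to select W&W". The other two fifths (40%) are taken to choose local resection.
- Later radical surgery: 20% after W&W, 40% after local resection.

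**Step 1, the plan's intermediate figures.** W&W = 40% + 0.60 × 20% = 52%. Local resection = 0.40 × 20% = 8%. Both match the printed values.

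**Step 2, the endpoint as defined.** 52% + 8% = 60%.

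**Step 3, later resections.** 0.20 × 52% + 0.40 × 8% = 10.4% + 3.2% = 13.6%.

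**Step 4, ultimate preservation.** 60% − 13.6% = 46.4%. The article prints 45.4%, which its own inputs do not reproduce. To reach 45.4% would need later surgery in 52.5% of local-resection cases (1 − (45.4 − 41.6)/8) or in 21.9% of W&W cases (1 − (45.4 − 4.8)/52). This one-point difference should be reconciled, but the present point does not depend on it.

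**Step 5, size of the gap.** 13.6 points, or 14.6 against the printed figure. As a share of those counted as not resected, 13.6/60 = 23%. If all planned patients were eligible, the numbers would be:

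- n = 105: 63 counted as not resected, about 14 of them later resected (105 × 0.136 = 14.3).
- n = 40: 24 counted, about 5 later resected (40 × 0.136 = 5.4).

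**Step 6, sensitivity.** The later-surgery rates are planning figures. If they are assumed to lie between 10% and 30% after W&W and between 30% and 50% after local resection, the gap runs from 0.10 × 52 + 0.30 × 8 = 7.6 points to 0.30 × 52 + 0.50 × 8 = 19.6 points.

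**Step 7, the offset in the other direction.** The remaining 100% − 60% = 40% of patients all count as resected under the definition. Some may never be resected, for instance because distant metastasis ends protocol treatment. The article gives no figure. If a share *u* of these 40% is never resected, the gap between the defined proportion and the true proportion without resection is 13.6 − 40*u* points: 9.6 at an assumed *u* of 10%, 5.6 at 20%, and zero only at 34% (13.6/40).

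**The case against.** The strongest reply is that the definition does not expressly keep resected patients in the numerator. It speaks of patients treated with W&W or local resection, not of patients started on them, and given the endpoint's name it could be read as meaning W&W or local resection instead of rectal resection. A journal article also condenses a full protocol, where a time point may be given. This stands in part: the article states no rule that resected patients count as preserved. But it does print a definition, and the literal wording, the missing time point and the off-protocol status of surgery after W&W all lead to the same count.

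Second, later resections are not lost. Phase III has rectal resection-free survival and colostomy-free survival, and stoma status and anal function are recorded at regular intervals. This stands, and it is the main reason the point is moderate. A reader might infer that the trial as a whole will overstate organ preservation; the article does not support that, because nothing says this proportion will carry the long-term claim.

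Third, a reader might infer that the 87% survival threshold was justified by the inflated figure. The article does not support that either. The threshold rests on about half of patients avoiding radical surgery, which is nearer to 45–46% or 52% than to 60%, and the Discussion itself subtracts later resections before stating expected preservation.

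Fourth, few later resections will be visible in phase II. The phase II primary analysis falls 6 months after enrolment ends, whereas the fourth response evaluation is placed at 40 weeks from the start of treatment. This stands. The gap will be smaller in phase II, where a change of name is enough.

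**Conclusion.** The point holds as a mismatch between the name and the definition of one secondary endpoint. On the article's own planning assumptions the defined proportion is 60% and ultimate preservation 46.4% (45.4% as printed), an overstatement of about 14 points before the unquantified offset from patients never resected for other reasons. The size rests on the literal reading of the definition and on the assumed rates of later surgery. The bias is not purely upward, since the definition errs in both directions. No primary endpoint, sample size or decision rule depends on this proportion. Severity is moderate: it should be corrected before results are reported, but it does not undermine the trial.

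**What to change.** One of two wording changes is enough.

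- In phase III, define the endpoint as the proportion of all eligible patients with no rectal resection, on or off protocol, by a fixed time point such as 5 years. State how death or loss to follow-up before that time is handled. This also classifies correctly the patients who are never resected for other reasons.
- Alternatively, keep the definition and rename the endpoint as the proportion managed initially with W&W or local resection, and take any statement about preservation from rectal resection-free survival.

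In phase II, use the renamed version under either option, because follow-up is too short for later resections to show. The 45.4% in the Discussion should be reconciled with its inputs at the same time.

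The cost is small. Resection dates are already needed for rectal resection-free survival, and no treatment rule, sample size or primary analysis changes. The downside for the sponsor is a less favourable reported preservation figure.
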